**Fig. 1 fig1:**
[figure not shown]
Working model of PTSD with an emphasis on immunomodulatory factors in the etiology and pathophysiology of PTSD. The model includes the influence of pre-existing factors that contribute to individual variability in physiological and psychological responses to trauma, leading to development and persistence of PTSD in a subset of individuals. Abbreviations: ANS, autonomic nervous system; HPA, hypothalamic-pituitary-adrenal; PTSD, posttraumatic stress disorder.

The goal of this Phase IIa placebo-controlled randomized controlled trial (ClinicalTrials.gov Identifier: NCT04150380) is to investigate the effects of daily oral administration of LGG (ATCC 53103) in a cohort of OEF/OIF/OND Veterans with PTSD as assessed by the gold standard Clinician Administered PTSD Scale-5 (CAPS-5) [44] who also have Functional Bowel Disorders (FBD), including irritable bowel syndrome. Outcomes include plasma concentration of high-sensitivity CRP (mechanistic, primary), and PTSD symptom severity (clinical, exploratory) [45]. Additional biological signatures will be considered exploratory. The primary hypothesis is that those who receive LGG supplementation will respond with lower plasma levels of CRP as compared to those allocated to a placebo supplement. Exploratory hypotheses include, as compared to those allocated to placebo, those who receive LGG supplementation will respond with: 1) decreased PTSD symptoms; 2) increased abundance of LGG and community-level shifts (e.g., increased alpha diversity) in the gut microbiota (measured using RT-qPCR and DNA sequencing of the 16S rRNA gene, respectively), decreases in IP (decreased fatty acid binding protein 2 [FABP2] and D-amino acid oxidase [DAO]), increases in plasma concentrations of anti-inflammatory biomarkers (IL-10, IL-4), decreases in additional plasma biomarkers of inflammation (IL-6, IL-8, IFNγ, IL-1α, IL-1β, and IL-12p70), reduced stress responsivity (biological and psychological) during and after participation in the Cyberball task, and improved decision-making (measured by performance on the modified Iowa Gambling Test [mIGT]); and, 3) the effect of LGG supplementation on stress responsivity, decision-making, and PTSD symptom severity will be mediated by effects of LGG supplementation on the gut microbiota, IP, and plasma biomarkers of inflammation.

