### Study design

2.1

The described Phase IIa trial will examine the effects of supplementation with LGG, a probiotic with anti-inflammatory and immunoregulatory properties, using a longitudinal, double-blind, randomized placebo-controlled design. It is expected that up to 215 Veterans will participate in initial evaluation procedures, with 118 being randomized to one of two interventions (probiotic or placebo supplementation; see Consort Diagram, Fig. 2). Randomization will be stratified by sex. This study is being conducted according to the guidelines outlined in the Declaration of Helsinki and all procedures involving human participants were approved by the Colorado Multiple Institutional Review Board (COMIRB).

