### Outcome measures

2.5

The primary mechanistic outcome for this study is plasma concentration of high-sensitivity CRP. Exploratory outcomes include: 1) PTSD symptom severity (PTSD Symptom Checklist for DSM-5; PCL-5) [47]; 2) type and abundance of LGG and community-level gut microbiota (measured using qRT-PCR and DNA sequencing of the 16S rRNA gene); 3) IP (FABP2 and DAO; 4) plasma concentrations of IL-10, IL-4, IL-6, IL-8, IFNγ, IL-1α, IL-1β, and IL-12; 5); biological and psychological stress responsivity during and after participation in the Cyberball task [48]; and, 6) decision-making (mIGT). All outcomes are listed in Table 2.

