### Study modifications during COVID-19 pandemic

2.7

Given challenges associated with in-person research due to the COVID-19 pandemic, the PIs made approved study modifications that allowed for continuance of the trial. Specifically, we modified T3 to include remote strategies both in terms of the stressor and strategy for measuring heart rate variability (HRV). This included switching from our original stressor, the Trier Social Stress Test [49] to Cyberball [48], which is a virtual ball-toss game that can be used for research on ostracism, social exclusion, or rejection. During Cyberball, the participant is told that they are playing a computerized ball tossing game with three other players over the internet: in reality, the other ‘players’ characters are controlled by the computer. After a few initial trials where the other players toss the ball to the participant, the other players then exclude the participant, only throwing to one another. This exclusionary experience has been found to be distressing to participants [50].

For HRV measurement, we will use the Firstbeat Bodyguard 2 (BG2) [51]. BG2 is a beat-to-beat heart rate monitoring device that is intended for short-term or long-term monitoring of heart rate variability and physical activity. The device records ECG with electrodes, processes the signal with an integrated algorithm and provides beat-to-beat R-to-R interval as an output with 1 ms resolution. The device easily attaches directly to the skin with two chest electrodes and starts recording data automatically. The BG2 has been designed for 24 h recordings. R-to-R timing data is downloaded from the BG2 to a computer for further analysis using standard HRV analysis software.

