The recruitment goal for this study is 59 participants per group. Anticipating a 15% attrition rate, we will have 50 participants per group for the final analysis. For the primary outcome of plasma concentration of CRP inflammatory biomarker, linear regression will be used to model the changes between T2 and T3, as a function of group, sex, the baseline value of CRP and any potential confounders identified as noted above. A similar analysis will be performed for the exploratory clinical outcome of PTSD symptoms (PCL-5 score). For the gut microbiome, linear regression will be used to model the changes between T2 and T3 both in alpha diversity, measured by Shannon Diversity Index, and in the gut microbiota community, quantified by Unweighted and Weighted UniFrac [54], pairwise distance between times for each individual, as a function of group, sex, the baseline value of the outcome, and potential confounders. Linear regression will also be used to model changes between T2 and T3 in IP (fatty acid binding protein 2 [FABP2], D-amino acid oxidase [DAO]), as well as plasma biomarkers of inflammation (IL-6, IL-10, IFNγ, IL-1α, IL-1β, IL-12p70, IL-8, and IL-4), and decision making as a function of group, sex, the baseline value of the outcome, and potential confounders. For stress outcomes from Cyberball (HRV, visual analog scale [VAS] and psychological stress measure [PSM]), linear regression will be used to model each outcome at T3 as a function of group. For each outcome measured at T2 and T3, the estimated mean difference in change between the groups will be reported with 95% confidence intervals (CI). For the stress outcomes measured only at T3 the estimated mean differences between the groups at T3 will be reported with 95% CIs. For the mediation analysis, we will use methods proposed by VanderWeele et al. for multiple mediators [55,56], examining whether the relationships between probiotic treatment and the outcome measures (PTSD symptoms, stress response, decision making) are mediated by changes in the gut microbiome, IP, and inflammation.

Assuming a CRP standard deviation of 1.19 mg/L as observed in Brenner et al. [40], 50 participants per group provides 85% power to detect a difference in change between groups of 0.73 mg/L at the α = 0.05 level for the primary outcome.

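### The Cyberball stress models leave out sex, the stratification factor, and show no pre-task reference for the hypothesised stress responsivity

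*Protocol article*

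**What the plan says.** Section 2.1 (Study design): "Randomization will be stratified by sex".

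Section 2.8 (Data analysis) gives covariates model by model:

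- CRP change is modelled "as a function of group, sex, the baseline value of CRP and any potential confounders identified as noted above", and PCL-5 receives a similar analysis.
- Microbiome, intestinal permeability, cytokine and decision-making changes use the same set. The last of these reads "decision making as a function of group, sex, the baseline value of the outcome, and potential confounders".
- For the Cyberball outcomes (HRV, VAS, PSM), "linear regression will be used to model each outcome at T3 as a function of group". The estimate to be reported is then fixed: "For the stress outcomes measured only at T3 the estimated mean differences between the groups at T3 will be reported with 95% CIs".

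The hypothesis in the Introduction is "reduced stress responsivity (biological and psychological) during and after participation in the Cyberball task". Section 2.5 (Outcome measures) names the outcome as "biological and psychological stress responsivity during and after participation in the Cyberball task". The mediation sentence in section 2.8 lists stress response among its outcomes.

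**The concern.** There are two separate matters.

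**Sex.** These outcomes have no T2 value, which explains why this model has no baseline term. It does not explain the missing sex term, since sex is known for every participant and is the factor by which they were randomised. This is more than silence left to a fuller document, because the article lists the terms of each model and gives this one a single term. When allocation is balanced within a prognostic stratum and the stratum is left out, the model counts between-sex variation as residual error. The standard error is then too large for the design.

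**Reference point.** Responsivity is a reaction relative to something. The model as written contains no pre-task term, and the reported estimate is a mean difference at T3. If the analysed variable were a raw level, a difference between arms in resting state could be reported as a difference in reaction to the stressor, and the same variable would enter the mediation analysis.

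**Working it through.** **The plan's own figure.** The only power statement concerns CRP: 50 per group, difference 0.73 mg/L, SD 1.19 mg/L, two-sided alpha 0.05, 85% power. The standardised effect is 0.73/1.19 = 0.613. Multiplied by sqrt(50/2) = 5, this gives 3.067, and 3.067 − 1.960 = 1.107, so power is 86.6% (85.9% with the noncentral t). The stated 85% reproduces. So does 59 per group, since 50/0.85 = 58.8. Neither figure bears on this point, and the article gives no power, SD or correlation for HRV, VAS or PSM. What follows rests on stated assumptions.

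**Cost of leaving out sex.** Inputs: 50 per group, sex balanced between arms by the stratification, R² = share of outcome variance due to sex (assumed), true effect 0.5 SD (assumed), normal approximation. In SD units the model-based SE without sex is sqrt(2/50) = 0.2, while the true SE is 0.2 × sqrt(1 − R²).

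- Actual alpha without sex = 2 × [1 − Φ(1.96/sqrt(1 − R²))]
- Power without sex = Φ[(0.5 − 1.96 × 0.2)/(0.2 × sqrt(1 − R²))]
- Power with sex = Φ[0.5/(0.2 × sqrt(1 − R²)) − 1.96]

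| Assumed R² | Actual alpha, sex omitted | Power, sex omitted | Power, sex included | Loss (points) |
|---|---|---|---|---|
| 1% | 0.049 | 70.6% | 71.0% | 0.4 |
| 5% | 0.044 | 71.0% | 72.7% | 1.7 |
| 10% | 0.039 | 71.5% | 75.0% | 3.5 |
| 15% | 0.034 | 72.1% | 77.4% | 5.3 |

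The intervals are too wide by a factor 1/sqrt(1 − R²), which is 1.005 at R² = 1% and 1.085 at 15%. The direction is always conservative.

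**What a pre-task reference would change.** Let r be the assumed correlation between pre-task and task values with equal SDs. Relative to the SD of the level, the SD of a change score is sqrt(2(1 − r)), and the residual SD after adjusting for the pre-task value is sqrt(1 − r²). The change-score factor equals 1 at r = 0.5. With 50 per group, a 0.5 SD effect on the task value and none on the resting value:

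| Assumed r | Level | Change score | Adjusted for pre-task value |
|---|---|---|---|
| 0.3 | 70.5% | 56.1% | 74.6% |
| 0.5 | 70.5% | 70.5% | 82.3% |
| 0.7 | 70.5% | 89.8% | 93.8% |
| 0.8 | 70.5% | 97.7% | 98.6% |

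If instead the arms differ only in resting level, by 0.2, 0.3 or 0.5 SD, and not in reaction, a test of level rejects 17%, 32% or 71% of the time. Adjustment does not fully remove this. With equal shifts s before and during the task, the adjusted contrast is s − r × s = s(1 − r), for example 0.5 × 0.3 = 0.15 SD at r = 0.7. The difference score gives zero.

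**The case against.** A reader might infer that the plan tests stress level instead of responsivity. The literal model wording and the fixed estimate lean that way, and section 2.8 speaks explicitly of change wherever it means change between visits. The documents do not establish it. Section 2.5 names the outcome itself as responsivity, and the mediation sentence calls it stress response. The Introduction describes the team's pilot measure as a stress-induced rise in heart rate, which is a within-session change. Naming T3 may simply identify the visit, because there is no T2 value. How the variable is derived may be set out in the full protocol or analysis plan, which is not shown. So this part stands only as a lack of clarity in the stated model.

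A reader might also infer from section 2.7 that a resting HRV segment exists: "The device easily attaches directly to the skin with two chest electrodes and starts recording data automatically". That describes the device. It does not say when the device is attached relative to the task, and no section mentions a pre-task VAS or PSM rating. It is therefore not shown that the data collected allow a more precise analysis.

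Nor can a large power gain be claimed. It appears only at high assumed correlations. At r = 0.5 a change score gains nothing, and below that it loses power. If supplementation leaves resting values unchanged, randomisation makes the T3 level difference an unbiased estimate of the effect on reaction. If supplementation does change them, a pre-task value taken after about 8 weeks of supplementation is a post-randomisation variable, and adjusting for it changes what is estimated.

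Finally, the outcomes are exploratory, and the CRP analysis already includes sex and baseline. This limits the weight of the point but does not answer the omission of sex.

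**Conclusion.** The omission of sex is established by the text and is minor. It causes neither bias nor type I inflation. The cost is a slightly conservative test and slightly wide intervals, of the size tabulated above, conditional on the assumed 1% to 15% of variance due to sex, a 0.5 SD effect, 50 per group and balance within strata.

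On responsivity, the supportable conclusion is limited: as written, the model has no pre-task reference, so the article does not show that it estimates the stated hypothesis. How much this matters cannot be determined from the article, because it depends on whether a pre-task value is recorded, on its correlation with the task value, and on whether supplementation shifts resting level.

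**What to change.** 1. Add sex to the Cyberball regressions in section 2.8, and to the stress-response models in the mediation analysis. This is a wording change that uses one degree of freedom and data already held.
2. State how each T3 stress variable is derived.
   - If the session records a pre-task value, analyse within-session reactivity (task or post-task relative to pre-task) on group and sex. Note that the pre-task T3 value is itself post-randomisation, and that a simple change score gains precision only if the pre/post correlation exceeds 0.5.
   - If no pre-task value is recorded, keep the T3 value and describe the result as a difference in stress level during or after the task, not as a difference in responsivity.
3. Use the same definition in the mediation analysis.

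None of this needs a new visit or procedure, because the reactivity analysis applies only where a pre-task value is already collected. The choice should be fixed before unblinding.

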## Discussion

3

Military personnel's recent exposures in Iraq and Afghanistan have resulted in a new generation of Veterans with persistent symptoms of PTSD. Moreover, stressors associated with the COVID-19 pandemic have placed both patients [57] and health care providers [58] at risk for developing trauma-related disorders. As such, novel means of intervention are required. In particular, efficacious interventions that are portable, non-stigmatizing, and cost-effective, such as probiotics, would be welcome.

As highlighted above, nonresponse rates in outcomes studies of PTSD have been notably high [7]. Schottenenbauer et al. explored possible predictors of nonresponse and dropout and highlighted the writing of Hembree and Foa, which suggested that those who need therapy the most have the greatest likelihood of dropping out or not responding to care [59]. In response, some have suggested that a subset of individuals may benefit from pre-treatment (e.g., skills training) to decrease dropout. However, Hembree and Foa also noted that dropout appears to be at least in part related to the complexity of treatment [60]. An alternate means of addressing this challenge would be to introduce an intervention, such as probiotics, that could alter patterns of autonomic activity during exposure to stressful experiences [40]. This strategy may facilitate sustained treatment engagement, even during periods in which the content of material being discussed during sessions is distressing.

Moreover, efforts outlined as part of this clinical trial are aimed at increasing understanding regarding inflammation, the gut microbiome, autonomic functioning (i.e., HRV), and PTSD symptoms. Such knowledge is expected to highlight multiple potential interventions for PTSD, as well as other mental health-related conditions that involve inappropriate inflammation and dysregulated autonomic function, for example long-COVID [61]. Also of note, Reber et al. recently completed an animal study in which mice were treated with a heat-killed preparation of an immunoregulatory environmental microorganism, *Mycobacterium vaccae* NCTC 11659 [62]. Findings showed that animals that were treated with *M. vaccae* NCTC 11659 were significantly more resistant to stress-induced pathology, thereby suggesting that immunoregulatory microorganisms may also have a role in preventing trauma-based disorders [62].

## Conclusions

4

In summary, the study outlined above is expected to provide low risk of bias data regarding the effects of LGG on multiple outcomes, including inflammation and PTSD symptoms. Given the increasing rate of PTSD, as well as current limitations of efficacious and frequently implemented treatments, these results are expected to provide evidence to inform alternate means of addressing the needs of the wide range of individuals living with or at risk for developing trauma-related conditions.

## Data Availability

No data were used for the research described in the article.
